# Enteral versus parental nutrition after pancreaticoduodenectomy under enhanced recovery after surgery protocol: study protocol for a multicenter, open-label randomized controlled trial (ENE-PAN trial)

**DOI:** 10.1186/s13063-022-06856-y

**Published:** 2022-10-29

**Keywords:** Pancreaticoduodenectomy, Enteral nutrition, ERAS

## Abstract

**Background:**

Infectious complications are the main causes of morbidity after pancreaticoduodenectomy (PD). Early enteral nutrition (EN) is a reasonable form of nutritional support that aims to mitigate the occurrence and severity of infectious complications by maintaining gut immunity. However, it remains unclear whether EN is beneficial for patients who underwent PD and are under enhanced recovery after surgery (ERAS) protocol.

**Methods:**

A multicenter (six hospitals), open-label, randomized controlled trial will be started in July 2022. A total of 320 patients undergoing open PD will be randomly assigned to an EN group or a peripheral parental nutrition (PPN) group in a 1:1 ratio. The stratification factors will be the hospital, age (≥ 70 or not), and preoperative diagnosis (pancreatic cancer or not). In the EN group, enteral nutrition will start on postoperative day (POD) 1 at 200–300 ml/day via the percutaneous tube placed operatively. The volume of the diet will be increased to 400–600 ml/day on POD 2 and depend on the surgeon’s decision from POD 3. In the PPN group, PPN will be delivered after surgery. In both groups, oral feeding will start on POD 3. Each treatment will be finished when patients’ oral food intake reaches 60% of the nutritional requirement (25–30 kcal/day). The primary endpoint will be the occurrence of postoperative infectious complications within 90 days of surgery. The secondary endpoints will be all complications, including major ones such as Clavien–Dindo grade 3 or more and clinically relevant postoperative pancreatic fistula. Data will be analyzed per the intention to treat.

**Discussion:**

This will be the first, large, and well-designed RCT that aims to determine whether EN is beneficial for patients who underwent PD under the ERAS protocol. According to the results of this study, either EN or PPN would be adopted as the standard nutritional support for patients undergoing PD.

**Trial registration:**

jRCT1030210691. Registered on March 23, 2022.

## Administrative information

Note: the numbers in curly brackets in this protocol refer to SPIRIT checklist item numbers. The order of the items has been modified to group similar items (see http://www.equator-network.org/reporting-guidelines/spirit-2013-statement-defining-standard-protocol-items-for-clinical-trials/).

## Introduction

### Background and rationale {6a}

Pancreaticoduodenectomy (PD) is a high-risk surgical procedure for patients with pancreatic head cancer and distal bile duct cancer. Despite advancements in surgical techniques and perioperative management, the morbidity rate remains high at 65–71% [1, 2]. Infectious complications, including postoperative pancreatic fistulas (POPFs) and organ surgical site infection, are the main causes of the morbidity and are sometimes life-threatening [3, 4]. To mitigate the occurrence and severity of infectious complications, several approaches, such as nutritional support, have been evaluated in many studies [1, 5–7].

Enteral nutrition (EN), which is easy to perform, is the most recommended postoperative artificial nutritional support for patients who undergo PD [8]. For patients with catabolic stress such as those who just underwent major surgery, early feeding via the enteral route could be a proactive therapeutic strategy that reduces the rate of infectious complications by helping to favorably modulate the immune response [9]. The underlying beneficial mechanism of EN is the presence of a physiological and immunological barrier, which could be impaired rapidly by starvation (“nil by mouth”) even when patients receive adequate parental nutrition [10].

Therefore, early EN was identified as reasonable management to mitigate the occurrence of infectious complications after PD; however, its benefits have been controversial so far. Previously, Grizas reported that early EN decreased the rate of infectious complications after PD more than peripheral parenteral nutrition (PPN) did [11]. On the other hand, Perinel showed that EN did not decrease the infectious complication rate more than total parenteral nutrition (TPN) did and that EN was associated with increased overall morbidity [1]. However, these randomized controlled trials (RCTs) had some problems in their sample sizes or postoperative management execution, such as the delayed restart of oral feeding. Recently, enhanced recovery after surgery (ERAS), including the early restart of feeding that aims to shorten the patient’s hospital stay without increasing the morbidity or readmission rates, has been accepted as standard perioperative management for patients undergoing PD [12]. This management could minimize the duration of starvation and prevent the impairment of gut immunity. Therefore, we designed a multicenter RCT to determine whether EN decreases the infectious complication rate after PD more than PPN does under the ERAS protocol.

### Objectives {7}

This study aims to investigate whether EN reduces the rate of postoperative infectious complications in patients undergoing PD and the ERAS protocol.

### Trial design {8}

The ENE-PAN trial is a randomized controlled, parallel-group, open-label, multicenter, superiority trial investigating the effectiveness of EN versus PPN after PD under the ERAS protocol. Eligible patients will be randomized equally to either the EN or the PPN group.

## Methods: participants, interventions, and outcomes

### Study setting {9}

The study is an investigator-initiated, multi-institutional, two-arm, open-label randomized trial in six Japanese academic hospitals. The flowchart of the trial is shown in Fig. 1.

**Fig. 1 Fig1:**
[figure not shown]
Consolidated Standards of Reporting Trials (CONSORT) flowchart. PD, pancreaticoduodenectomy; EN, enteral nutrition; PPN, peripheral parental nutrition

### Eligibility criteria {10}

The inclusion criteria are below:Age ≥ 20 yearsIndication for elective PDAmerican Society of Anesthesiologists performance score of 1–3Written informed consent given by the patient

The exclusion criteria are as follows:Robot-assisted or laparoscopic PDCombined liver resectionAntibiotic therapy within a week before surgeryContraindications for EN (allergy, disorder of amino acid metabolism, etc.)Severe cardiac, liver, or renal comorbiditiesPatient judged to be ineligible for enrolment by the investigator

### Who will take informed consent? {26a}

Potential participants will be identified from patients who visit hospitals. After assessment by surgeons regarding inclusion and exclusion criteria, the trial information will be given to potential participants in person by surgeons. Written and verbal informed consent will be obtained. The right of a participant to refuse to participate in the study without giving reasons for the decision will be respected.

### Additional consent provisions for collection and use of participant data and biological specimens {26b}

Patients included in the study will be offered the opportunity to participate in an ancillary study investigating the survival of patients. Consent for participating in the ancillary study will be obtained when the study starts.

## Interventions

### Explanation for the choice of comparators {6b}

There is poor evidence as to which form of nutritional support is the best at present. The international study group of pancreatic surgery recommends the early resumption of oral intake in the ERAS protocol [8]. According to a review article, early mandatory postoperative TPN is not associated with improved outcomes [13].

### Intervention description {11a}

The patients included in the study will undergo open PD on day 0 and be randomized to a PPN (control) group or an EN (experimental) group.

In the PPN group, PPN will be delivered after surgery. In the EN group, EN will start on postoperative day (POD) 1 at 200–300 ml/day via the percutaneous tube placed operatively. The volume of the diet will depend on the capacity per back nutritional supplements used at each hospital. This volume will be increased to 400–600 ml/day on POD 2, and the volume from POD 3 will be decided by surgeons. Surgeons will select enteral formulas such as Elental® (EA pharma corporation), K-5S® (NUTRI corporation), and Pepucino® (Terumo corporation) based on their preference. The feeding jejunostomy catheter will be inserted through the jejunum wall and fixed using the Witzel Technique before closing the wound.

In both groups, oral solid feeding will start on POD 3. The total calories of food provided by hospitals are shown, and nurses will record the amount of food consumed by patients. Each treatment will be finished when patients’ oral food intake reaches to 60% of the nutritional requirement (25–30 kcal/day) [1]. The percutaneous tube will be removed at the bedside per the surgeon’s decision after the patient’s oral food intake attains the requirements.

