### Criteria for discontinuing or modifying allocated interventions {11b}

Any patient requesting to end their participation in the study can be withdrawn from the study regardless of the stage they have reached in the study process. Patients do not have to provide the reason of withdrawal. Patients found to be pregnant or those judged ineligible to continue participating in the study by the investigators will also be withdrawn from the study.

In the EN group, the volume of the diet will be decreased if patients suffer from diarrhea that is not cured by antidiarrheal agents. TPN will be delivered if patients’ oral intake in the PPN group is less than 200 kcal/day on POD 14.

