## Data collection and management

### Plans for assessment and collection of outcomes {18a}

Case report forms are constructed as web-based forms (REDCap) and data entry will be conducted by surgeons or trained medical personnel. Baseline patient characteristics will include the age, sex, height, weight, hand grip strength, psoas mass index, comorbidity, preoperative diagnosis, preoperative treatment (neoadjuvant chemotherapy, antibiotics, biliary drainage, nutritional support), preoperative laboratory variables (white blood cell count, hemoglobin concentration, serum total protein, serum albumin, serum transferrin, serum pre-albumin, C-reactive protein), and the American Society of Anesthesiologists physical status.

Surgical data will include the surgical procedure, method of reconstruction, remnant pancreas texture, diameter of the main pancreatic duct, operation time, estimated blood loss, and need for a blood transfusion.

Postoperative data will include patients’ clinical conditions, morbidities and their severity, the mortality rate, length of hospital stay, time to functional recovery from surgery, laboratory data, cost, and any side effects. In patients with pancreatic cancer, the time to the introduction of adjuvant chemotherapy from surgery will also be measured. All patients will be followed up at each hospital for at least 90 days.

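### The rule for ending EN and PPN rests on a requirement printed as 25–30 kcal/day, which puts the cut-off at 15–18 kcal/day; the unit is wrong, probably through a dropped per-kilogram term

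*Protocol article*

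**What the plan says.** Intervention description {11a} sets the end of treatment for both arms at the point where oral intake reaches "60% of the nutritional requirement (25–30 kcal/day"). The Methods part of the abstract gives the same rule with the same unit: "Each treatment will be finished when patients’ oral food intake reaches 60% of the nutritional requirement (25–30 kcal/day").

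Two other statements in {11a} bear on the rule. Intake is measured per patient: "The total calories of food provided by hospitals are shown, and nurses will record the amount of food consumed by patients". The feeding tube comes out at the surgeon's discretion once "oral food intake attains the requirements".

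The section on discontinuing or modifying allocated interventions {11b} has a second intake threshold, for the PPN arm only: "TPN will be delivered if patients’ oral intake in the PPN group is less than 200 kcal/day on POD 14".

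Body weight is among the baseline data in {18a}: "Baseline patient characteristics will include the age, sex, height, weight, hand grip strength". No section of the article expresses the requirement per kilogram or defines it in any other way.

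**The concern.** A daily requirement of 25–30 kcal cannot describe a whole patient, and 60% of it is smaller still. Since the same unit stands in the abstract and in the operative section, the reader has no correct version to fall back on.

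The number matters because it is the only numerical criterion for ending EN and PPN, and so it defines how long the experimental and the control treatment last. Oral solid food starts on POD 3 in both arms. Followed literally, the rule would end both treatments at almost the first food eaten. The tube-removal sentence also refers back to the requirement. The monitoring centre is asked to verify that the protocol is followed, and the printed figure gives it no workable standard for when treatment should have stopped.

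**Working it through.** The article states the requirement and the percentage but no resulting threshold, so there is no derived figure to reproduce. The check computes the threshold under each reading and compares it with the other intake threshold in the article.

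**Inputs**

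- Fraction of the requirement: 60% ({11a} and abstract).
- Requirement as printed: 25–30 kcal/day ({11a} and abstract).
- Intake below which TPN starts in the PPN group on POD 14: 200 kcal/day ({11b}).
- Body weights of 40, 60 and 80 kg: my assumption, for illustration only.

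**As printed**

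- Lower end: 0.60 × 25 = 15 kcal/day.
- Upper end: 0.60 × 30 = 18 kcal/day.
- Ratio to the TPN threshold: 200 / 18 = 11.1 and 200 / 15 = 13.3.

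A PPN patient eating anywhere from 18 to just under 200 kcal/day would therefore have met the rule to finish PPN and, on POD 14, would also qualify for TPN. One protocol cannot mean both that such intake is sufficient and that it is inadequate.

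**If the unit is kcal/kg/day (assumption)**

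Threshold = 0.60 × 25 to 0.60 × 30 = 15 to 18 kcal/kg/day, multiplied by body weight:

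| Assumed weight | Lower end (15 × weight) | Upper end (18 × weight) |
|---|---|---|
| 40 kg | 600 kcal/day | 720 kcal/day |
| 60 kg | 900 kcal/day | 1080 kcal/day |
| 80 kg | 1200 kcal/day | 1440 kcal/day |

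The weight above which this cut-off exceeds 200 kcal/day is 200 / 15 = 13.3 kg at the lower end and 200 / 18 = 11.1 kg at the upper end. Every adult is above both. On this reading the stopping rule always lies above the TPN threshold, so the two rules agree.

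The clash with {11b} is thus a consequence of the unit error, not a second fault.

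**The case against.** The strongest reply is that this is a misprint nobody could act on. The figure is so far from any patient's daily need that a clinician would read it as per kilogram, and an impossible number is less dangerous than a plausible wrong one. The operative phrase is the percentage of the requirement. The bracket only glosses it, and {11a} cites a source for the rule that is not available here. The article condenses a fuller protocol, and the working copy at the sites may carry the right unit. Tube removal is left to the surgeon in any case. Nothing inferential depends on the number.

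Much of this stands, and it limits the consequence. The sample size, the primary outcome and the intention-to-treat comparison do not use the figure, and nothing in the article shows hospitals reading it differently. The 11- to 13-fold gap is evidence that the unit is wrong; it does not measure harm.

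The reply does not rescue the printed text, though. It asks the reader to replace a stated criterion with one that is not stated. This is also not a detail that an article may leave to the full protocol: the article gives the number, gives it twice, and gives it wrongly. And a reader who supplies the missing per-kilogram term still has to guess which weight applies.

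**Conclusion.** The concern holds. As printed, the threshold for ending EN and PPN is 15–18 kcal/day, which cannot be a whole-patient value and is 11.1 to 13.3 times below the intake that {11b} treats as inadequate. That conclusion rests on the article alone.

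The explanation, a lost per-kilogram term, is an inference that the article does not confirm. The 600–1440 kcal/day range rests on that inference and on assumed weights of 40 to 80 kg.

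This is one unit error in a treatment-defining rule, repeated in two places. It should be corrected because it is the only numerical stopping criterion in both arms. It has no effect on the sample size or the primary analysis.

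**What to change.** The sponsor should confirm the intended unit and correct it in the abstract and in {11a}. The most likely wording is 60% of a requirement of 25–30 kcal/kg/day. The same edit should state the reference weight; the baseline weight collected under {18a} would serve, but the article does not say which weight is meant, so the choice is the sponsor's. If the protocol used at the sites carries the same unit, it needs the same correction. The 200 kcal/day rule in {11b} can stay as it is.

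The cost is a wording change in two places. With baseline weight as the reference, no procedure, data item or analysis is added.

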### Criteria for discontinuing or modifying allocated interventions {11b}

Any patient requesting to end their participation in the study can be withdrawn from the study regardless of the stage they have reached in the study process. Patients do not have to provide the reason of withdrawal. Patients found to be pregnant or those judged ineligible to continue participating in the study by the investigators will also be withdrawn from the study.

In the EN group, the volume of the diet will be decreased if patients suffer from diarrhea that is not cured by antidiarrheal agents. TPN will be delivered if patients’ oral intake in the PPN group is less than 200 kcal/day on POD 14.

### Strategies to improve adherence to interventions {11c}

All treatments will be administered to participants during their stay in the hospital by attending surgeons; therefore, participants’ adherence to interventions is assured.

### Relevant concomitant care permitted or prohibited during the trial {11d}

All other treatments will be allowed.

### Provisions for post-trial care {30}

All patients who will suffer harm from trial participation will be covered by the Japanese public healthcare system and the insurance for this study.

### Outcomes {12}

The primary outcome of this study will be the infectious complication rate after PD. The secondary outcomes will be all postoperative complications; major complications (Clavien–Dindo grade > 3); clinically relevant POPF (CR-POPF); delayed gastric emptying (DGE); the length of hospital stay (LOS); time to functional recovery after surgery; serum levels of albumin, pre-albumin, and transferrin; the cost; side effects; and time to the introduction of adjuvant chemotherapy from surgery in patients with pancreatic cancer [14].

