### Sample size {14}

The sample size was calculated for a 15% absolute reduction in the postoperative infectious complication rate in the EN group based on a postoperative complication rate of 40% in the PPN group [11]. To achieve 80% power and a 95% significance level, 152 patients are required in each group. To compensate for the loss of participants to follow-up (0.5%), we plan for 320 patients (160 in each group) to be included in the study.

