A potential limitation of this study is that we will not be able to perform a double-blind study, and this limitation could affect our results; however, it could be minimized by using strictly defined diagnostic criteria for infectious complications and the Clavien–Dindo grading system. Another limitation is that concomitant treatments could affect some outcomes. However, no treatments have strong evidence to mitigate the primary outcome of our study. Although our study will be performed under the ERAS protocol, the ERAS protocol is not completely the same in six hospitals because each hospital has its own ERAS protocol. However, we have an agreement in the majority of current ERAS items such as preoperative smoking and fasting, epidural analgesia, postoperative glycaemic control, early removal of drains, early and scheduled mobilization, and early diet from postoperative day 3 [15].

This trial is the first large-scale, well-designed RCT to investigate whether EN is beneficial for patients undergoing PD under the ERAS protocol. According to the results of this study, either EN or PPN would be adopted as standard nutritional support for patients undergoing PD.

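### Major complications, a secondary outcome, exclude Clavien–Dindo grade 3 in Outcomes {12} but include it in the Abstract, and nothing in the article reconciles the two

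*Protocol article*

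**What the plan says.** Outcomes {12} is where the article formally lists its endpoints. It begins "The secondary outcomes will be all postoperative complications" and continues with "major complications (Clavien–Dindo grade > 3", followed by pancreatic fistula, delayed gastric emptying, length of stay and several others.

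The Methods paragraph of the Abstract summarises the same secondary endpoints as all complications, "including major ones such as Clavien–Dindo grade 3 or more", together with clinically relevant pancreatic fistula.

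The grading system is named once more, in the Discussion. There the authors argue that the limitation of an open-label design can be reduced by "strictly defined diagnostic criteria for infectious complications and the Clavien–Dindo grading system". No threshold is given there.

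**The concern.** A strict inequality at 3 and a threshold of 3 and above are different endpoints. The narrower one sits in the section a programmer or later reader would treat as authoritative. Someone who follows Outcomes {12} as written would leave out every patient whose worst event is grade 3; someone who follows the Abstract would count them.

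The consequence is a published plan under which two different event counts could each be described as prespecified. This matters somewhat more here than in a blinded trial. Participants and researchers know the allocation (Who will be blinded {17a}), surgeons or trained staff enter the data (Plans for assessment and collection of outcomes {18a}), and the Discussion relies on the grading system as part of its answer to that limitation.

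**Working it through.** The check is mainly textual.

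**1. The two definitions side by side.** The article does not print the scale, so I take the usual ordered grades 1 to 5, with sub-grades a and b within 3 and 4.

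| Place | Wording | Grades counted |
|---|---|---|
| Abstract, Methods | "major ones such as Clavien–Dindo grade 3 or more" | 3a, 3b, 4a, 4b, 5 |
| Outcomes {12} | "major complications (Clavien–Dindo grade > 3" | 4a, 4b, 5 |

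**2. The difference.** Let N3, N4 and N5 be the numbers of patients in an arm whose worst complication is grade 3, 4 or 5.

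- Abstract: N3 + N4 + N5
- Outcomes {12}: N4 + N5
- Difference: N3

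A patient with both a grade 3 and a grade 4 event counts under either definition. The disagreement is therefore exactly the patients whose worst event is grade 3. The article gives no value for N3, N4 or N5, so the difference cannot be turned into an expected count or rate.

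**3. Does anything else settle it?**

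- Plans for assessment and collection of outcomes {18a} records morbidities with their severity, without a threshold.
- Statistical methods {20a} names tests by type of variable only.
- The Discussion names the grading system without a threshold.

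No other section reconciles the two.

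**4. Could it be an artefact of reading the PDF?** This is unlikely. The ≥ sign is preserved elsewhere in the same text: in the age strata in the Abstract, in Eligibility criteria {10}, in Sequence generation {16a} and in the subgroup section {20b}.

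**5. Is the sample size affected?** Sample size {14} plans for "a 15% absolute reduction in the postoperative infectious complication rate in the EN group" from 40%, that is 40% against 25%, and states "To achieve 80% power and a 95% significance level, 152 patients are required in each group". With a two-sided alpha of 0.05, 80% power and no continuity correction:

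n = [1.960 × √(2 × 0.325 × 0.675) + 0.842 × √(0.40 × 0.60 + 0.25 × 0.75)]² / 0.15²

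= [1.960 × 0.6624 + 0.842 × 0.6538]² / 0.0225

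= (1.298 + 0.550)² / 0.0225 ≈ 151.9, so 152 per group.

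The stated figure is reproduced, and no Clavien–Dindo grade enters it.

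**The case against.** The best defence is that this is one mistyped symbol. The Abstract writes its cut-off in words, which is hard to do by accident, and nothing suggests that the sponsor wants an endpoint restricted to grades 4 and 5. The article also condenses a full protocol and case report form that are not shown and may carry the right threshold. Much of this stands: a slip is the likeliest explanation, and the article does not show that the trial will be analysed on the narrower definition. But the article states the threshold twice and the statements conflict. That is a contradiction, not a detail left to another document, and it sits in the section that defines the outcomes.

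Three stronger readings are tempting, and the article does not support them.

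- A reader might infer that a key secondary endpoint is at stake. Outcomes {12} lists about ten secondary outcomes and ranks none. The Abstract mentions major complications by name, but only as part of all complications.
- A reader might infer that the cut-off will be chosen once results by arm are known. Section {17a} says that data analysts will be blinded. Unblinded investigators could still settle the definition late, so the risk is reduced and not removed, but the article describes no such choice.
- A reader might argue that the narrower definition leaves the comparison with almost no power. Any such figure would rest on invented event rates and an invented effect. The trial is powered only for its primary endpoint, so low power on a secondary outcome is not in itself a planning error.

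**Conclusion.** The inconsistency is real, and Outcomes {12} cannot stand alongside the Abstract as both are written. It should be corrected, but its reach is small: one unranked secondary outcome, differing by the patients whose worst complication is grade 3. How many patients that is cannot be determined from the article. The primary endpoint is described as a set of seven infectious complications with their own diagnostic criteria, and the article ties it to no Clavien–Dindo cut-off; it and the sample size are unaffected.

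The conclusion rests on a literal reading of both statements and on the usual ordering of the grades. It needs no assumption about event rates. That > is a slip for ≥ is a probable inference from the Abstract's wording, not something the article states.

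**What to change.** Before any unblinded analysis, state one cut-off and use it identically in the Abstract, Outcomes {12}, the case report form and the analysis program. On the present text, the natural correction is to change Outcomes {12} to Clavien–Dindo grade ≥ 3. If the sponsor confirms that grades 4 and 5 alone were intended, correct the Abstract instead.

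The cost is one symbol, or one phrase in the Abstract, plus a check of the form and the program. No new data are needed, because the severity of complications is already collected under {18a}, and the sample size does not change.

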## Statistical methods

### Statistical methods for primary and secondary outcomes {20a}

An intention-to-treat analysis will be conducted to compare primary and secondary outcomes between the EN group and the PN group. Differences between the groups of patients will be analyzed via Fisher’s exact test (as appropriate) for categorical data and by Student’s *t*-test for continuous variables. *P-*values of less than 0.05 will be considered statistically significant. Statistical analyses will be performed using SPSS version 28 (IBM Corp., Armonk, NY, USA).

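### Albumin, pre-albumin and transferrin are measured before surgery, but the planned Student's t-test ignores those values and loses precision

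*Protocol article*

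**What the plan says.** Three sections of the protocol article bear on this point.

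- **Outcomes {12}** includes "serum levels of albumin, pre-albumin, and transferrin" in the list of secondary outcomes.
- **Plans for assessment and collection of outcomes {18a}** records the same markers before surgery, in the list of preoperative laboratory variables: "serum total protein, serum albumin, serum transferrin, serum pre-albumin, C-reactive protein". It also collects laboratory results after surgery: "time to functional recovery from surgery, laboratory data, cost, and any side effects".
- **Statistical methods for primary and secondary outcomes {20a}** sets the scope, "An intention-to-treat analysis will be conducted to compare primary and secondary outcomes between the EN group and the PN group", and gives one method for measurements on a continuous scale: Student's t-"test for continuous variables". The significance threshold is also fixed: "values of less than 0.05 will be considered statistically significant".

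The article does not mention covariate adjustment, ANCOVA, a mixed model or change from baseline. The postoperative sampling days are not given in the text; the assessment schedule is in Fig. 2, which is not reproduced in the text available here.

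**The concern.** A patient's albumin, pre-albumin or transferrin after surgery can be expected to depend partly on the level before surgery. A two-group t-test on the postoperative level does not use that information, with two consequences.

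1. The between-patient variation that the baseline value could explain stays in the standard error, so the confidence interval is wider than the collected data allow.
2. If the arms differ by chance at baseline, part of that difference carries through to the estimated treatment effect. Randomisation is stratified by hospital, age and diagnosis, and not by any nutritional marker, so the design does not limit such imbalance directly.

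The trial tests a nutritional intervention, and these three markers are the only listed outcomes that measure nutritional status in the laboratory. An imprecise comparison would make it harder to say whether enteral feeding changed nutritional status at all, whatever the result on infection.

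**Working it through.** **The plan's own figure.** The article gives no power calculation for the markers, so the group size comes from Sample size {14}, whose effect assumption reads: "15% absolute reduction in the postoperative infectious complication rate in the EN group based on a postoperative complication rate of 40% in the PPN group". The other inputs are 80% power and, as only this reproduces the figure, a two-sided 0.05 level. With p₁ = 0.40, p₂ = 0.25 and mean 0.325:

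n = [1.960·√(2 × 0.325 × 0.675) + 0.842·√(0.40 × 0.60 + 0.25 × 0.75)]² / 0.15²

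= [1.960 × 0.6624 + 0.842 × 0.6538]² / 0.0225 ≈ 151.9, so **152 per group**, as stated. This n is used below.

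**Baseline for comparison: the unadjusted t-test.** With 152 per group, the difference detectable with 80% power, in units of the outcome's standard deviation (SD), is

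d = √(2/152) × (1.960 + 0.842) = 0.1147 × 2.802 = **0.321 SD**.

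**ANCOVA on the preoperative value.** If r is the within-arm correlation between preoperative and postoperative levels, then:

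- residual variance relative to the t-test = 1 − r²
- detectable difference = 0.321 × √(1 − r²)
- power at 0.321 SD = Φ(2.802/√(1 − r²) − 1.960)
- t-test group size needed to match = 152/(1 − r²)

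The article gives no r, so the table shows a range of assumed values.

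| Assumed r | Variance ratio 1 − r² | Effective sample-size ratio 1/(1 − r²) | ANCOVA power at 0.321 SD | ANCOVA detectable difference (SD) | t-test n per group to match |
|---|---|---|---|---|---|
| 0.2 | 0.96 | 1.04 | 81.6% | 0.315 | 158 |
| 0.3 | 0.91 | 1.10 | 83.6% | 0.307 | 167 |
| 0.4 | 0.84 | 1.19 | 86.4% | 0.295 | 181 |
| 0.5 | 0.75 | 1.33 | 89.9% | 0.278 | 203 |
| 0.7 | 0.51 | 1.96 | 97.5% | 0.229 | 298 |

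With the planned 160 per group the ratios are the same. The t-test then detects 0.313 SD, and ANCOVA detects 0.299, 0.271 and 0.224 SD at r = 0.3, 0.5 and 0.7.

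**Effect of chance imbalance.** Assuming equal SDs before and after surgery, a baseline difference of b SD shifts the unadjusted estimate by r × b. The standard error of the baseline difference is √(2/152) = 0.115 SD. An imbalance of one standard error therefore shifts the t-test estimate by 0.3 × 0.115 = 0.034, 0.5 × 0.115 = 0.057 or 0.7 × 0.115 = 0.080 SD. ANCOVA removes this shift.

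**Would a t-test on change from baseline do instead?** Again assuming equal SDs, its variance relative to the plain t-test is 2(1 − r): 1.40, 1.00 and 0.60 at r = 0.3, 0.5 and 0.7. ANCOVA has 0.91, 0.75 and 0.51. Change scores are worse than the plain t-test below r = 0.5 and never better than ANCOVA.

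**The case against.** The strongest reply is that nothing here is invalid. Under randomisation the t-test is unbiased and holds its type I error rate, which already allows for chance imbalance. The markers are one entry in a long list of secondary outcomes, no power is claimed for them, and the article rests its rationale on gut immunity and infection and not on serum proteins. All of that stands, and it limits the importance of the point.

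The size of the gain is also unknown. Major surgery and unrestricted concomitant care lie between the two measurements, so a low correlation cannot be excluded; at r = 0.2 the variance falls by only 4%. This stands too. A low r shrinks the benefit but does not make adjustment harmful: the preoperative value costs one of 302 residual degrees of freedom (304 patients less two group means).

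Two further replies carry less weight. One is that section 20a might mean a t-test on change, which would use the baseline value. The outcome is worded as a level, change is not mentioned, and that analysis would still be no more efficient than ANCOVA. The other is that covariates are usually left to a statistical analysis plan. That would hold if the article were silent, but section 20a names the test and applies it to the primary and secondary outcomes, so an adjusted analysis would depart from the published method.

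**Conclusion.** The concern holds. The article fixes an unadjusted t-test for three outcomes whose preoperative values it already collects. The cost is lost precision and exposure to chance baseline imbalance; bias on average and false-positive error are not at issue. The t-test carries 1/(1 − r²) times the variance of ANCOVA: 1.19, 1.33 and 1.96 times at r = 0.4, 0.5 and 0.7, and 1.10 times at r = 0.3. These figures rest on an assumed correlation and a linear relation between baseline and follow-up. The primary outcome, its test and the sample size are not affected. This should be changed because the gain is free, but it does not threaten the trial's main conclusion.

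**What to change.** In section 20a, replace Student's t-test for these three markers with an ANCOVA of the postoperative value on treatment, the same marker's preoperative value, and the stratification factors (hospital, age group, preoperative diagnosis). If a marker is measured on several postoperative days, use a mixed model for repeated measures with the same covariates and name the day of main interest. Report adjusted mean differences with 95% confidence intervals.

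The cost is a change of analysis wording: the preoperative values are already in the case report form, and no patients, visits or samples are added. One detail should be settled at the same time. Section 20c rules out any statistical method for missing data, so a patient without a preoperative value would drop out of the ANCOVA. The plan should say how such a patient is handled. The change should be made before unblinded outcome data are available to the analysts.
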